### Participants and recruitment

Patients will be enrolled in the Department of Neurosurgery, Zuyderland Medical Center, Heerlen, the Netherlands. All adult patients indicated for single- or multi-level surgery for radiculopathy and/or myelopathy due to CDDD are eligible to be included in the study.

If patients choose not to participate in the study, the standard treatment, ACDF with stand-alone cage, will be offered. If patients agree to be included in the study, they will complete the informed consent form. ICGs will also be asked to participate, to enable a broad societal evaluation of costs. Patients can leave the study at any time for any reason without consequences. The investigator can decide to withdraw a patient from the study for urgent medical reasons. Since the sample size accounts for a 20% loss to follow-up, patients will not be replaced after withdrawal.

### Inclusion criteria

In order to be eligible to participate in this study, a patient must meet all of the following criteria:Indication for anterior cervical decompression surgerySingle- or multi-level CDDD, located between C3 and C7, with a maximum of 4 consecutive levelsSymptoms of myelopathy, radiculopathy, or myeloradiculopathyIn the case of pure radiculopathy: refractory to at least 6 weeks of conservative therapyIn the case of myelopathy, it must be symptomaticPatients ≥18 years of age

### Exclusion criteria

Patients who meet any of the following criteria will be excluded from participation in this study:Indication for (additional) posterior surgical approachIndication for additional stabilization of the pathological segment by a plate; in case there are sign of instability (e.g., spondylolisthesis) and additional stabilization is deemed necessaryPrevious surgery of the cervical spine (anterior and posterior)Traumatic origin of the compressionPrevious radiotherapy of the cervical spineMetabolic bone diseaseInflammatory spinal disease, e.g., Bechterew’s disease, Forestier’s diseaseInfection of the cervical spineUnable to fill out Dutch questionnairesInformed consent not possible

Dropout criteria include technical reasons related to placing either of the implants during the surgery. Other reasons for dropout are expected to be low.

### Interventions

One of two surgical procedures will be performed on patients participating in this study: ACDA (intervention group) and ACDF (control group). In both techniques, the disc space is approached through a right- or left-sided anterior surgical approach. The disc content will be removed, after which the endplates are prepared with curettes. The posterior longitudinal ligament is opened, and the dura is visualized to ensure adequate decompression. In the ACDF group, a cage (CeSPACE® XP) is implanted; in the ACDA group, a disc prosthesis (ActivC®) is implanted after the discectomy. No bone substitutes will be used.

Implantation of the devices is done in accordance with the manufacturer’s protocol for implantation and endplate preparation. In both groups, the wound is closed in layers, after a prevertebral wound drain is placed. Potential surgical risks are similar between the cage (ACDF) and the arthroplasty group (ACDA) [38, 61].

Post-surgical care is the same for both groups. Patients receive 24 h of antibiotic prophylaxis, and after 24 h, the prevertebral wound drain is removed. Patients can use analgesics post-operatively, and they are allowed to mobilize immediately. The day after surgery, a physical therapist provides patients with standardized exercises. Patients are not routinely referred to a physical therapist, and no neck collar is used.

### Implementation plan

Figure 1 depicts the flowchart of the study process. Patients will be selected by screening the appointments in the neurosurgical outpatient clinic the waiting lists for surgery. When a patient is indicated to undergo anterior cervical decompression surgery, the treating neurosurgeon will inform the patient about the CACES trial. The patient is contacted by the investigator to provide extensive information. Additionally, written information is sent to them by (e)mail. A week after the information is sent, the investigator contacts the patient again to answer remaining questions. Patients are included in the study when informed consent is signed. Data is collected in the research manager tool, which is a database with a built-in auditing system. Questionnaires, including reminders, are sent automatically once the patient is registered in Research Manager. If patients or informal caregivers prefer to fill out questionnaires on paper, the answers will be registered in Research Manager by the investigator and the paper version will be stored. Data will be collected at baseline and at 6-month intervals until 4 years post-surgery. The patients will be blinded to their received treatment for the first year after surgery to obtain more reliable patient-reported outcome measures (PROMs). After 1 year, patients will have an outpatient appointment with the coordinating investigator for unblinding (if wanted) and additional imaging.

**Fig. 1 Fig1:**
[figure not shown]
Study design. Timing of pre- and post-operative outcome measurements and follow-up evaluations

### Outcome measures

All outcomes will be measured at baseline and at 6-month intervals until 4 years post-surgery.

#### Primary outcome

The primary outcome is cost-effectiveness and cost-utility of ACDA compared to ACDF from a societal perspective, in patients with single- or multi-level CDDD and symptoms of radiculopathy and/or myelopathy. The primary outcome will be evaluated at 4 years post-operative.

The economic evaluation will involve a combination of a cost-effectiveness analysis (CEA) and cost-utility analysis (CUA) from a societal perspective. In the CUA, the effects are presented as quality-adjusted life years (QALYs), based on the EuroQol 5 dimensions 5 levels (EQ-5D-5L) [62] utility scores [63]. The Net Monetary Benefit (NMB) will be determined, in which effect is expressed in QALYs. The incremental cost-effectiveness ratio (ICER) will be expressed as the incremental costs per QALY. This economic evaluation will be conducted according to the Dutch Guidelines of the National Health Care Institute [64–66]. The following validated cost questionnaires will be used: Productivity Cost Questionnaire (iPCQ) [67] and the Medical Consumption Questionnaire (iMCQ) [67]. These questionnaires allow a broad measurement of societal costs, including medical consumption, and both paid and unpaid loss of productivity for patients. ICGs will be asked to fill out the Limited Valuation of Informal Care Questionnaire (iVICQ) [68], which consists of the Care-related Quality of Life instrument (CarerQol-7D) and the Self-Rated Burden scale (SRB). This measures the (subjective) burden for ICG and the assessment of caregiving in terms of wellbeing.

#### Secondary outcomes

Secondary outcomes will consist of both clinical and radiological outcome measurements.

Clinical outcomes will be assessed according to the rate of CASP and associated additional surgeries, combined with patient-reported outcome measures (PROMs). The included PROMs are the Neck Disability Index (NDI) [69], Visual Analogue Scale (VAS) [70] for neck and arm pain, Hospital Anxiety Depression Scale (HADS) [71], and the modified Japanese Orthopedic Association score (mJOA) [72] for myelopathy or myeloradiculopathy patients. CASP is defined as the presence of newly developed symptomatic cervical radiculopathy and/or myelopathy on a level adjacent to the initial surgery, confirmed by corresponding findings upon magnetic resonance imaging (MRI). It should be noted that *RASP* is differentiated from *CASP* by the presence of clinical symptoms that are attributed to the degenerative changes for the latter. Patients were only considered as having CASP when new clinical symptoms developed. Additional adjacent segment surgery for CASP was defined as surgery for radiculopathy and/or myelopathy at a segment adjacent to the level of initial surgery. Notably, neck pain itself is not considered as a surgical indication in our national guidelines [73]. Re-operations at the index level and at levels not adjacent to the initially operated level were not considered as additional surgery for CASP.

Radiological outcomes will be assessed at three time points: pre-operative, directly post-operative, and 1 year post-operative. Pre-operative imaging will assess baseline degeneration according to the Kellgren-Lawrence Score (KS) [74], cervical sagittal alignment, and baseline disc height. Moreover, a full sagittal spine X-ray will be taken to assess pre-operative global balance according to the odontoid-hip axis (OD-HA) [75]. A standard cervical spine X-ray will be taken at the immediate post-operative period (before discharge) to assess the position of the implant, subsidence, and cervical sagittal alignment. Cervical spine X-rays will be taken again 1 year post-operative to assess fusion, cage subsidence, adjacent segment degeneration (KS), adjacent segment disc height, and alignment. A flexion and extension X-ray will be taken to assess movement. Radiological cage subsidence will be defined as > 3-mm decrease of interbody height compared to the direct post-operative X-ray [76, 77].

Moreover, a process evaluation will be performed to determine the underlying values, needs, impacts, and preferences of people with CDDD. The focus will be on the experiences and opinions of patients, caregivers, and professionals concerning the process surrounding ACDA and ACDF. A process evaluation might also identify gaps or limitations in the published research with regard to important outcomes to those with lived experience. A qualitative analysis will be performed according to the framework provided by Saunders et al. [78].

#### Covariates

Per-operative parameters such as intraoperative complications, operative time, size of the implant, and blood loss will be evaluated. Perioperative complications, re-operations at index- or non-adjacent levels, and their associated costs will be assessed.

### Power considerations

The primary outcome of the proposed study is cost-effectiveness. No difference in QALYs is expected between the intervention and control groups based on previous literature [41].

The only expected difference in clinical effectivity is the additional adjacent segment surgery rate, with an average of 1.0% versus 2.2% (Table 1). Although small, a difference in additional surgery rates is present in all trials, increasing exponentially over the years. We believe that the small inter-group difference may result in a cost-effective intervention, mainly because we expect most of the difference in costs to arise from episodes of secondary symptoms, which can lead to absenteeism, use of analgesic medication, use of (para)medical supplies, and additional adjacent segment surgery.

Reported additional adjacent segment surgery rates for ACDA vary from 0 to 2.8% per year, with an average of 1.0% based on the largest FDA/IDE trials [46, 79]. As for ACDF, yearly reported additional adjacent segment surgery rates range from 0 to 4.2%, with an average of 2.2% [80, 81].

The cost of a cervical disc prosthesis for ACDA is estimated to be around €2000, while the cage for an ACDF costs €500, resulting in a difference of €1500 per implant. Based on our data from the past years, on average, 1.2 implants are used per procedure.

Hospital admission costs and procedural costs are similar for both procedures, which is estimated to be €11,000 in our center. As reported by ArboNed for the year 2019, the average absenteeism for cervical disc pathology was 242 days, with a standard deviation of 225 *[personal communication]* [82]. The average cost for 1 day of absenteeism varies between €200 and €400, depending on salary and company; for example, 1 day of absence from work is usually calculated to cost around €250 in the Netherlands *[personal communication]* [82].

In the Netherlands, the willingness to pay (WTP) threshold for spinal pathologies — classified as a moderate disease — is set at €50,000/QALY [65, 66]. However, in the sample size calculation, we will not fix WTP at one value. The sample size calculation is based on both QALYs and costs, using Net Monetary Benefit (NMB) as outcome. The NMB for a treatment is defined as [83]:$$NMB= WTP\times Effect- Costs$$

The smallest relevant effect in terms of NMB will be quantified in terms of Cohen’s *d*, which is defined as:

$$d=\frac{average\ NMB\ (ACDF)- average\ NMB\ \left(\mathrm{ACDA}\right)}{Standard\ deviation\ of\ NMB}$$

The standard classification of Cohen’s *d* consists of a small effect (*d* = 0.2), a medium-sized effect (*d* = 0.5), and a large effect (*d* = 0.8) [84].

A two-sided test will be used with a 5% level of significance (*α* = 0.05). A Cohen’s *d* of 0.4 is often referred to as the hinge point, meaning a greater than average effect [84]. We expect a bit less than a medium-sized effect, for which we choose a Cohen’s *d* in between 0.5 and 0.4, resulting in a Cohen’s *d* of 0.45. Inclusion of 79 patients per treatment group will then yield a power of 0.80. Taking into account a 20% loss to follow-up in 4 years, the required sample size is 99 per group, with a total of 198 patients.

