## Article summary

### Strengths and limitations of this study

External validity and generalizability are limited, as costs are country-specific.A broad economic analysis from a societal perspective in the setting of a prospective randomized controlled trial will investigate the cost-effectiveness of ACDA and ACDF for CDDD, resulting in level I evidence.The sample size is based on estimated costs and average yearly incidence of CASP, which may differ from reality.The burden for patients in this study is low, and potential risks in the intervention group (ACDA) are similar to those in the control group (ACDF with stand-alone cages), which is standard care in our center.Since the gap in incidence of additional CASP-related surgery between ACDF and ACDA expands considerably with time, we expect that a difference in costs, if found within the 4-year follow-up period, will also increase over time.

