## Methods

### Objectives

The primary objective of the proposed study is to examine whether ACDA is preferred over ACDF in terms of cost-effectiveness from a healthcare and societal perspective, in patients with single- or multi-level symptomatic CDDD. Secondary objectives include differences in clinical and radiological outcomes between the two techniques, as well as the qualitative process surrounding anterior decompression surgery.

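### The stated power of 0.80 holds only at a conventional Cohen's d of 0.45; the protocol's own average inputs imply a far smaller effect, with power of roughly 5–19%

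*Protocol article*

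**What the plan says.** Power considerations in the Protocol article sizes the trial on NMB, with the effect expressed as Cohen's d. "A two-sided test will be used with a 5% level of significance". The section introduces d as the smallest relevant effect, but justifies the value as an expectation: "We expect a bit less than a medium-sized effect". It then takes the midpoint of 0.4 and 0.5, "resulting in a Cohen’s *d* of 0.45", and concludes: "Inclusion of 79 patients per treatment group will then yield a power of 0.80". Allowing for 20% loss gives 99 per group and 198 in total.

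The same section sets out what the investigators expect. On effects: "No difference in QALYs is expected between the intervention and control groups based on previous literature". On events and costs, it lists adjacent segment surgery rates, implant prices, a procedure cost, and the length and daily cost of work absence. On the threshold: "However, in the sample size calculation, we will not fix WTP at one value". None of these figures appears in the step that yields 0.45.

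The article summary nevertheless states: "The sample size is based on estimated costs and average yearly incidence of CASP, which may differ from reality". The Discussion repeats this as a limitation. It also says that no similar studies exist from which to estimate effect sizes, and that the sample size may therefore be too large or too small.

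**The concern.** A reader told that the size comes from estimated costs and CASP incidence will take 0.80 as the chance of detecting the difference those estimates predict. The section shows that it is the chance of detecting a conventional effect size. If the listed inputs predict a much smaller standardised difference, the trial is far less likely to reach significance than it appears, even if arthroplasty (ACDA) does save money as hypothesised. A non-significant result would then be read as coming from a trial with 80% power, when it would carry little information about the hypothesis.

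**Working it through.** **Reproducing the stated figures.** A two-sample t test, two-sided α = 0.05, d = 0.45 and 79 per arm gives power 0.803. Dropout: 79 / 0.80 = 98.75, so 99 per arm and 198 in total. All reproduce.

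**Inputs**
- Power considerations: QALY difference 0; surgery rates 1.0% (ACDA) and 2.2% (ACDF) a year; €11,000 per admission and procedure; absence of 242 days (SD 225) at €200–400 a day, usually about €250; 1.2 implants × €1,500 = €1,800 extra for ACDA.
- Primary outcome: 4 years. Event probabilities are therefore 4 × 1.0% = 4.0% and 4 × 2.2% = 8.8%, a difference of 4.8 points.
- Introduction: 50–75% of CASP patients need surgery, so 1.33 to 2 episodes per surgery. I used m = 1 (only the surgical episode causes absence) to m = 2.

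**Expected difference.** With no QALY difference, the expected NMB difference equals the cost difference at any willingness to pay. For daily cost w:

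Δ = 0.048 × (11,000 + m × 242 × w) − 1,800

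- Low (w = 200, m = 1): 0.048 × 59,400 − 1,800 = €1,051
- Central (w = 250, m = 1): 0.048 × 71,500 − 1,800 = €1,632
- High (w = 400, m = 2): 0.048 × 204,600 − 1,800 = €8,021

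**SD of NMB.** The protocol gives none, so I assumed two.
- (a) Event-only: variation from these episodes alone. In the central case the variance per arm is p × (71,500² + 56,250²) − (p × 71,500)², where 56,250 = 225 × 250. This gives SD 26,244 at p = 0.088 and 17,969 at p = 0.04, pooled √[(26,244² + 17,969²)/2] = €22,490. For m = 2, half the episodes carry the surgery cost.
- (b) Absenteeism SD for all patients: 225 × w.

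**Implied d (size of the advantage to ACDA) and power at 79 per arm**

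| €/day | m | Δ (€) | SD (a) | d | power | SD (b) | d | power |
|---|---|---|---|---|---|---|---|---|
| 200 | 1 | 1,051 | 18,410 | 0.057 | 6.5% | 45,000 | 0.023 | 5.2% |
| 250 | 1 | 1,632 | 22,490 | 0.073 | 7.4% | 56,250 | 0.029 | 5.4% |
| 250 | 2 | 4,536 | 29,750 | 0.152 | 15.9% | 56,250 | 0.081 | 8.0% |
| 400 | 2 | 8,021 | 46,740 | 0.172 | 18.8% | 90,000 | 0.089 | 8.6% |

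**What 0.45 SD means in euro.** 0.45 × 22,490 = €10,120; 0.45 × 56,250 = €25,313. These are 6.2 and 15.5 times €1,632. For €1,632 to equal d = 0.45, the SD would have to be 1,632 / 0.45 = €3,627.

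**Extremes of the reported rates.** For 0% versus 4.2% a year the difference is 16.8 points. At €250 and m = 1: 0.168 × 71,500 − 1,800 = €10,212; event-only SD 24,961; d = 0.41; power 72%. Over €200–400 and m = 1 to 2, d is 0.40 to 0.65 with SD (a) and 0.18 to 0.36 with SD (b).

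**Friction cost method.** Statistical analysis values productivity loss this way, which limits the absence counted; the friction period is not stated. At €250 and m = 1 the saving is zero at (1,800 / 0.048 − 11,000) / 250 = 106 counted days. For illustration, 60 days gives 0.048 × 26,000 − 1,800 = −€552, and 120 days gives 0.048 × 41,000 − 1,800 = +€168. The SD would shrink as well, so the table cannot be carried over unchanged to the planned analysis scale.

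**The case against.** The strongest reply is that the calculation is correct and conditional: 0.80 is claimed at d = 0.45, and power at a target difference is not refuted by a smaller expected difference. The arithmetic part stands. A reader might go further and infer that the 0.80 belongs to no defined quantity because willingness to pay is left open. That is not supported. It belongs to 0.45 SD of NMB, and with no expected QALY difference the threshold alters the SD but not the expected difference. The target-difference defence is weaker, because the section also calls 0.45 expected and gives no reason why some €10,000 or more should be the smallest relevant amount.

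Second, the protocol does not supply every input, as a reader might assume. The SD is missing. Analgesics and (para)medical supplies are named as cost drivers without figures, as are unpaid productivity and informal care under Primary outcome. So the d values are conditional on my SDs. But to lift €1,632 to €10,120, these items would have to add 10,120 − 1,632 = €8,488 per randomised patient, before their own variance is counted. The event-only SD is already generous: it leaves out QALY variance, index-episode absence and all other costs.

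Third, 0.17 is the best case only at the average rates. The extremes of the reported ranges come near or above 0.45 with the event-only SD, but they are not what the protocol says it expects.

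Fourth, the Discussion admits that the size may be over- or underestimated. That is fair disclosure of uncertainty, but it does not tell the reader what the listed inputs imply.

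Finally, a reader might infer that a null result would, under the Discussion, settle the matter for fusion (ACDF). It would not. That passage requires the study to show that ACDF is the more cost-effective, which a non-significant test does not do.

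**Conclusion.** The point holds as a fault in the effect-size assumption and its description; the sample size arithmetic itself is right. The power of 0.80 applies only to a conventional d of 0.45. The statements in the article summary and Discussion that the size rests on estimated costs and CASP incidence are wrong as they stand. At the protocol's average inputs the expected difference is about €1,050 to €8,000 (central €1,632), d is about 0.02 to 0.17, and power with 79 per arm is about 5% to 19%.

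This rests on two assumed SDs, on every episode causing a full paid-work absence, and on one or two episodes per surgery. It counts the full absence. Under the friction cost method the expected saving would be smaller, and zero or negative if fewer than about 106 days per event are counted at €250. The gap to 0.45 is large enough that the conclusion does not depend on the exact SD.

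**What to change.** Keep N = 198 and restate the power paragraph:
- Say that 79 per arm gives power 0.80 for a difference of 0.45 SD of NMB, that 0.45 is a conventional value, and what it is in euro under a stated SD, with productivity valued by the friction cost method. The full-absence figures above should not be printed as final.
- Say that the protocol's own average inputs imply a far smaller effect, with power of roughly 5–19% or lower.
- Say that a non-significant test would not be evidence against ACDA, and base interpretation on the incremental NMB with its 95% CI. Statistical analysis already plans effect sizes with intervals.
- Correct the sentences in Strengths and limitations and in the Discussion to say that the sample size rests on a conventional effect size.

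The cost is wording and one recalculation on the friction cost scale, with no extra patients. The downside is that the stated power becomes much less favourable.

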### Statistical analysis

All statistical procedures will be conducted based on both the intention-to-treat principle and on actual participation in treatment (i.e., per-protocol analyses) and will be performed using SPSS statistics (SPSS, IBM, Corporation, Chicago, USA). Effect sizes and their 95% confidence intervals will be estimated. A two-sided significance level of 0.05 will be used as a threshold to determine whether differences are statistically significant. Trends in differences between ACDA and ACDF will be measured over time. If significant differences are found, post hoc analyses further investigate these effects.

Costs will be calculated by multiplying volumes (resource use) with unit costs. For the unit costs, we will use the Dutch costing guidelines. Productivity costs will be calculated by means of the friction cost method, based on a mean added value of the Dutch working population. Cost prices (2022) will be expressed in euros. If necessary, existing cost prices will be updated using the consumer price index (2022).

